#### ***Stabilometry***

The participants will remain barefoot on a force plate (Biomec 400 v1.1^®^, EMG System Ltda^®^ - http://www.emgsystem.com.br - [name]. [name]) consisting of four load cells with an internal circuit that changes in electrical resistance upon the application of force (dimensions: 1 m × 1 m; sampling frequency: 100 Hz). The participants will stand with unrestricted width of the foot base, heels in alignment, arms alongside the body and gaze fixed on a circular target (5 cm in diameter), at the height of the glabellum, attached to a pedestal at a distance of two meters.

The stabilometric data will be recorded during quiet standing for 70 seconds under two visual conditions: eyes open (EO) and eyes closed (EC). Data collection will be carried out under each condition, with a one-minute rest between trials, during which time with subjects will be allowed to sit.

#### ***Surface EMG***

Surface EMG signals from the right and left masseter and right and left anterior temporal bundle will be recorded with disposable surface electrodes (Ag/AgCl - Noraxon^®^ - http://noraxon.com - [name]. [contact]) attached to the belly of the muscle in the region with the greatest tonus after the volunteer performs moderate intercuspation (clenching of the teeth). The inter-electrode distance will be 20 mm from center to center. The sites for the electrodes will be cleaned with a cotton ball soaked in alcohol to diminish the impedance between the skin and electrodes [39]. A rectangular metallic electrode measuring 3 cm × 2 cm coated with Lectron II conductive gel (Pharmaceutical Innovations^®^ - http://www.pharminnovations.com - [name] [name]) to increase the conduction capacity and impede interference from external noise will be attached to the left wrist of the volunteers for reference.

The bipolar EMG signals will be amplified using an eight-channel module (EMG System do Brasil Ltda^®^ - http://www.emgsystem.com.br - [name]. [name])) consisting of a conditioner with a band pass filter with cut-off frequencies of 20 to 1000 Hz, an amplifier gain of 1,000 and a common mode rejection ratio > 120 dB. All data will be acquired and processed using a 16-bit analog to digital converter (EMG System do Brasil Ltda^®^ - http://www.emgsystem.com.br - [name]. [name])) at a sampling frequency of 2 kHz.

For the recording of the EMG signals, the participants will remain seated in a chair with feet apart and hands resting on the lower limbs. To standardize the EMG potentials of the four muscles analyzed with tooth contact, two strips of Parafilm M^®^ (American National Can TM, Chicago, IL, USA) will be folded into five parts (3 mm in thickness) and positioned on the first and second mandibular molars (bilateral) of each subject [40]. Four seconds of maximum voluntary clenching (MVC) will be recorded three times, with a three-minute interval between readings.

After five minutes of rest, the recording of EMG activity will be performed three times successively under the following conditions: i) rest position: the subjects will be asked to relax and maintain the maxillary and mandibular teeth without contact; ii) maximal intercuspation (isometric): the subjects will be ask to clench the teeth as hard as possible and maintain the same level of contraction (tooth contact); and iii) chewing (isotonic): the subjects will be instructed to mildly and symmetrically bite down (chew) on the two strips of Parafilm M^®^ (positioned bilaterally) in time with a metronome adjusted to 60 beats per minute.

For the EMG signals recorded in rest position and during chewing, a two-minute interval will be allowed between readings. For maximal intercuspation, a five-minute interval between readings will be used. The data collection time will be 15 seconds for the rest position and chewing condition and 8 seconds for maximal intercuspation.

#### ***Massage and mobilization interventions***

The participants will be divided into three groups, each of which will be submitted to a different protocol. Ten sessions will be given for each treatment.

Protocol 1: massage therapy, described in Table 2; the procedure will last for 20 minutes and consist of synchronized sliding and kneading with medium pressure on the anterior temporal and masseter muscles bilaterally.

Protocol 2: nonspecific mandibular mobilization with the participant in dorsal decubitus on a cot, performed by a previously trained, experienced therapist wearing disposable gloves, who will position the fifth finger on the last molar, performing nonspecific mandibular mobilization, grade I [41], intermittently for one minute, with five repetitions. In the interval between repetitions, the participant will perform mouth opening 15 times with the tongue on the incisive papilla.

Protocol 3: specific mandibular mobilization with the participant in dorsal decubitus on a cot, performed by a previously trained, experienced therapist wearing disposable gloves, who will position the fifth finger on the last molar of the side being treated and ask the participant to lightly bite down on the finger, at which point the therapist will perform specific mandibular mobilization for the disk with reduction or without reduction:

For disk with reduction, pressure to be applied will be in the caudal direction and the oscillation will be cranial to caudal, grade I [41], intermittently for one minute, with five repetitions. In the interval between repetitions, the participant will perform mouth opening 15 times with the tongue on the incisive papilla;

For disk without reduction, pressure to be applied will also be in the caudal direction and the oscillation will be caudal to cranial, grade I [41], intermittently for one minute, with five repetitions. In the interval between repetitions, the participant will perform mouth opening 15 times with the tongue on the incisive papilla.

**Table 2 T2:** Twenty-minute facial massage protocol performed bilaterally

	
Surface sliding	3 minutes
Circular movements in counter-clockwise direction	
Anterior bundle of temporal muscle	
Kneading	3 minutes
Kneading in cranial-caudal direction	
Upper fibers of masseter muscle	
Return of hands to initial position with continuous caudal-cranial sliding of suprahyoid musculature	
Surface sliding	1 minute
Circular movements in counter-clockwise direction	
Anterior bundle of temporal muscle	
Kneading	1 minute
Kneading in cranial-caudal direction	
Upper fibers of masseter muscle	
Return of hands to initial position with continuous caudal-cranial sliding of suprahyoid musculature	
Surface sliding	1 minute
Circular movements in counter-clockwise direction	
Anterior bundle of temporal muscle	
Kneading	1 minute
Kneading in cranial-caudal direction	
Upper fibers of masseter muscle	
Return of hands to initial position with continuous caudal-cranial sliding of suprahyoid musculature	
Deep sliding	3 minutes
Circular movements in counter-clockwise direction	
Anterior bundle of temporal muscle	
Kneading	3 minutes
Kneading in cranial-caudal direction	
Upper fibers of masseter muscle	
Return of hands to initial position with continuous caudal-cranial sliding of suprahyoid musculature	
Deep kneading	1 minute
Circular movements in counter-clockwise direction	
Anterior bundle of temporal muscle	
Kneading	1 minute
Kneading in cranial-caudal direction	
Upper fibers of masseter muscle	
Return of hands to initial position with continuous caudal-cranial sliding of suprahyoid musculature	
Deep sliding	1 minute
Circular movements in counter-clockwise direction	
Anterior bundle of temporal muscle	
Kneading	1 minute
Kneading in cranial-caudal direction	
Upper fibers of masseter muscle	
Return of hands to initial position with continuous caudal-cranial sliding of suprahyoid musculature	
Finalization with light touch	

In protocols 2 and 3, the side of the mandible to be mobilized will be previously defined through the diagnosis performed with the RDC/TMD; depending on the diagnosis, one or both sides of the mandible may be mobilized. The therapist will remain standing on the contralateral side to the mandibular mobilization, thereby avoiding any pressure on the mandible and exclusively performing millimeter mandibular movements.

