Studies have suggested that massaging the muscles of mastication, joint mobilization, manual therapy, mandibular exercises, biofeedback and the application of electrophysical resources may be effective in the treatment of TMD [22-26]. Joint mobilization has proven effective at reducing pain, disability and local ischemia [27], breaking fibrous adhesions, enhancing the extensibility of non-contractile structures, increasing the range of motion, enhancing the transmission of afferent information through the stimulation of mechanoreceptors and stimulating proprioception and the production of synovial fluid [27,28]. The use of joint mobilization has been tested on individuals with TMD, in whom a reduction in pain and increased mandibular range of movement (ROM) have been reported [29-32].

Massage has proven effective at diminishing EMG activity and pain [19,21], preventing the formation of connective tissue adherences, enhancing the production and circulation of endogenous opioids [19], increasing local blood flow, facilitating the elimination of residual substances and extracellular fluid, improving the nutrition of myofibrils and promoting relaxation and a sensation of wellbeing [33,34]. Massaging the muscles of mastication has been administered to patients with TMD, leading to a reduction in pain, an increase in mandibular ROM and a decrease in EMG activity in the muscles [21,35].

Postural control may be related to afferent signals of the trigeminal nerve, which depend on information from receptors of the stomatognathic complex (dentoalveolar ligaments, muscle and joint receptors). Moreover, TMD may alter muscle activity and the positioning of structures of the stomatognathic system, interfering in the information transmitted for the control of posture. Thus, relaxation of the muscles of mastication (as assessed through surface EMG) and the alignment of joint structures (assessed through a clinical exam) may alter afference from the receptors of the stomatognathic system, thereby affecting postural control (assessed through stabilometry). Based on this hypothesis, the aim of the proposed study is to determine the effect of facial massage and mandibular mobilization on EMG activity of the muscles of mastication and static balance in individuals with TMD.

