## Methods/Design

### Overview of research design

A randomized, controlled, blind, clinical trial is proposed to study the effects of specific and nonspecific mandibular mobilization. The participants will be allocated to three groups through a randomization process using opaque envelopes. Each group will receive a specific form of treatment for TMD. The control group (CG) will receive massage therapy and those submitted to joint mobilization will be divided into two groups: the specific mobilization group (SMG) and the nonspecific mobilization group (NMG). Evaluations will be carried out before and after treatment using the Research Diagnostic Criteria for Temporomandibular Disorders (RDC/TMD), EMG of the masseter and temporal muscles and stabilometry.

After screening, individuals with TMD (based on the RDC/TMD) will be selected. The study will be divided into three types of treatment, three evaluations and two phases, to which all individuals will be submitted:

Evaluation 1: randomization of treatment with allocation to treatment groups, stabilometric analysis and EMG analysis, with the administration of the protocol for the respective treatment.

Evaluation 2: second stabilometric and EMG evaluation immediately following respective treatment.

Treatment phase: treatment following respective protocol.

Evaluation 3: third stabilometric and EMG evaluation and second administration of the RDC/TMD questionnaire.

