## Discussion

The main objective of the proposed study will be to assess the effect of mandibular mobilization using surface EMG and stabilometric variables. Numerous studies have substantiated the reliability and reproducibility of surface EMG in the evaluation of the muscles of mastication [42-45], which was the main criterion for the choice of this measure to calculate the sample size for the proposed study, and especially to investigate the possible effects of the two techniques for the treatment of TMD.

Regarding CoP measurements, however, it is not yet possible to determine whether stabilometric variables offer adequate reproducibility in patients with TMD. The reliability of CoP variables has generally been analyzed in healthy adults and elderly individuals [60] or those with associated diseases [61,62], but no such studies are found involving patients with TMD. This led to the need to conduct the aforementioned pilot study to test the reproducibility of the data and determine the collection protocol for the stabilometric variables idealized in the project. The preliminary execution of this project also contributed to an adjustment of the data collection protocol regarding the number of trials per session based on the participants’ reports of discomfort, as described above.

Studies have demonstrated that the number of recorded tests exerts an effect on the reliability of CoP measurements used to assess postural control during quiet standing (static posture) [60-63]. Although the results of this study indicate that CoP-based measurements have quite diverse levels of reliability, mean velocity was the most reliable measure with regard to within-day and between-day readings, which is consistent with earlier reports [46,60,61,63,64]. Within-day reliability was generally better than between-day reliability. Moreover, the reliability of CoP measurements was also influenced by the visual condition (eyes open and eyes closed). The ICC was greater under the eyes open condition for mean velocity and median frequency (ƒ80) in the two directions (AP and ML). The visual influence on postural control demonstrates a specific characteristic among individuals with TMD, as higher overall reliability values have previously been demonstrated under the eyes closed condition compared to eyes open [49,65,66].

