The weakest index regarding reliability was the SaEn, followed by sway area. The variation in ICC among poor, fair and good and the high SEM demonstrate that these variables should not be considered when investigating the possible effects of mandibular mobilization for the treatment of TMD.

The results of this pilot studied showed that mean velocity was the most reliable measure, which is consistent with earlier reports, and can be selected as a reliable postural sway measure. Moreover, the results of the proposed study will help determine whether specific and/or nonspecific mandibular mobilization exerts an effect on the muscles of mastication and postural control. Moreover, if an effect is detected, the methodology defined in the proposed study will allow identifying whether the effect is local (found only in the muscles of mastication), global (found only in postural control) or generalized.

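### Both mobilization arms also receive a mouth-opening exercise that the massage arm does not, so contrasts with the control group estimate a package against massage, not mobilization alone

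*Protocol article*

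**What the plan says.** The Overview of research design sets up three arms: "The control group (CG) will receive massage therapy and those submitted to joint mobilization will be divided into two groups", specific (SMG) and nonspecific (NMG).

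The section on massage and mobilization interventions describes what each arm receives, and fixes the course: "Ten sessions will be given for each treatment".

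- **Control group (CG), Protocol 1.** Massage only: "the procedure will last for 20 minutes and consist of synchronized sliding and kneading with medium pressure on the anterior temporal and masseter muscles bilaterally". Table 2 itemises it step by step.
- **NMG, Protocol 2.** Grade I mobilization, "intermittently for one minute, with five repetitions", followed by this instruction: "In the interval between repetitions, the participant will perform mouth opening 15 times with the tongue on the incisive papilla".
- **SMG, Protocol 3.** The same timing and the same mouth-opening instruction, given separately for each of the two disk variants.

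The Background lists treatments that may help in temporomandibular disorder (TMD): "massaging the muscles of mastication, joint mobilization, manual therapy, mandibular exercises, biofeedback and the application of electrophysical resources may be effective". Joint mobilization, mandibular exercises and massage appear there as separate items. The aim at the end of the Background covers the effects of both facial massage and mandibular mobilization.

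The Discussion is narrower: "The main objective of the proposed study will be to assess the effect of mandibular mobilization using surface EMG and stabilometric variables". It expects the results to "help determine whether specific and/or nonspecific mandibular mobilization exerts an effect on the muscles of mastication and postural control", and the Discussion part of the Abstract says the same.

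**The concern.** The two mobilization arms differ from the control arm in two components, the manual technique and repeated active mouth opening, but the stated objective names only the first. If SMG or NMG differs from CG, the difference may reflect mobilization, the exercise, or both.

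On the protocol's own reasoning the exercise is not inert. The Background treats mandibular exercise as a possible therapy. It also traces mandibular proprioception to changes in mandible position and to movement of the condyles, and links that input to postural control. Active opening moves both the mandible and the condyles, so it could plausibly affect the electromyographic and the stabilometric outcomes. At Evaluation 2, which follows directly after treatment, mobilization participants will have done the openings shortly before measurement and massage participants will not.

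At stake is what the trial may claim. A favourable result would be reported as an effect of mandibular mobilization, and then classed as local, global or generalized, although the design does not isolate that component.

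**Working it through.** **1. Is the massage arm free of the exercise?** Table 2 states 20 minutes. Its timed steps, in order, are 3 + 3 + 1 + 1 + 1 + 1 + 3 + 3 + 1 + 1 + 1 + 1 = 20 minutes. The stated duration is reproduced, and every step is sliding or kneading applied by the therapist, ending with an untimed light touch. No active opening appears in the table or in the text of Protocol 1. Since the article sets out the massage minute by minute, the absence is not a product of condensing.

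**2. How much exercise do the mobilization arms get?** The inputs are five repetitions, 15 openings per interval and ten sessions, all from the interventions section.

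- Intervals between five repetitions: 5 − 1 = 4.
- Openings per session: 4 × 15 = 60.
- Openings over the course: 60 × 10 = 600.
- Control group: 0.

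This assumes one set of intervals per session. If a set also followed the fifth repetition, the figures would be 5 × 15 = 75 and 75 × 10 = 750. The article allows one or both sides to be mobilized and does not say whether the openings repeat for a second side, so the counts are approximate.

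**3. How large is the manual component beside it?** Mobilization is 5 × 1 = 5 minutes per session for a treated side, or 50 minutes over ten sessions. Massage is 20 × 10 = 200 minutes.

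**4. What does each contrast estimate?** Write S and N for the effects of specific and nonspecific mobilization, E for the exercise and P for massage. Assume additivity for simplicity, and let T be any change over time unrelated to treatment.

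| Comparison | Estimates |
|---|---|
| SMG − CG | (S + E) − P |
| NMG − CG | (N + E) − P |
| SMG − NMG | (S + E) − (N + E) = S − N |
| Change within SMG | S + E + T |
| Change within NMG | N + E + T |
| Change within CG | P + T |

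E cancels only in SMG − NMG. No row, and no combination of rows, gives S or N by itself, because every participant who is mobilized also exercises and no arm receives the exercise alone. Analysis cannot separate components that always occur together. Nor do randomization and blinding help, since the difference lies in the assigned treatments.

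If E were the same in all arms, the first row would become S − P. That is still an effect relative to massage, and the difference in treatment time would remain.

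**The case against.** The strongest reply is that the arms are openly defined as treatment protocols. The Overview assigns each group its own form of TMD treatment, and the openings are written inside Protocols 2 and 3. On this view the exercise is part of the technique, and the package is simply named after its main component. Randomization gives a valid comparison of that package with massage. The Background aim also includes facial massage, so the trial can be read as comparing active treatments. SMG versus NMG, which bears directly on the study of specific and nonspecific mobilization, is matched on the exercise.

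Much of this stands. The randomized comparison is sound for what is delivered, and the weakness is one of attribution. What does not stand is the label: no section defines the intervention as mobilization plus exercise, and the Background lists the two separately. Treating the mouth openings as an instance of the mandibular exercises listed there is a reasonable inference, though the article does not say so outright.

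Three stronger readings are tempting and are not supported.

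- A reader might infer that the whole of any difference from massage is due to the exercise. The documents give no figure for the effect of the exercise, so no share can be assigned to it.
- A reader might infer that the control group is untreated. Massage is an active comparator, which the Background describes as reducing electromyographic activity and pain.
- A reader might infer that equalising the exercise would by itself justify claiming an effect of mobilization against CG. The last step of the working shows why it would not.

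**Conclusion.** The point holds as one of attribution and should be fixed. SMG versus CG and NMG versus CG validly estimate mobilization plus mouth-opening exercise relative to 20 minutes of active massage. Neither contrast, nor any change within a mobilization arm, can credit mobilization alone, as the Abstract and Discussion intend. SMG versus NMG is the only contrast in which the exercise is balanced. It compares the two types of mobilization as delivered (Protocol 3 also includes a light bite on the therapist's finger) and cannot show that mobilization as such has an effect.

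The imbalance is about 60 openings per session and 600 over ten sessions against none, assuming four intervals and one set of intervals per session. Its presence does not depend on the count: any exercise confined to the mobilization arms has the same consequence. How much it affects the outcomes cannot be derived from the documents.

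**What to change.** Change the wording of the objective and intended conclusions in the Abstract and the Discussion:

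1. Define the intervention in SMG and NMG as *mandibular mobilization plus mouth-opening exercise*.
2. Report SMG versus CG and NMG versus CG as effects of that package relative to massage, and describe massage as an active comparator that is itself part of the Background aim. Apply the same package label to changes within the mobilization arms and to the classification of effects as local, global or generalized.
3. State that SMG versus NMG is the only contrast in which the exercise is balanced, and that it compares types of mobilization only.

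The cost is a narrower claim. No procedures or participants are added, and the treatment protocols are left as they are. The trial is recruiting, so the wording can be settled before results are read.
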